### Identifying Cases and Controls

#### Cases

Cases will be women and first-borns enrolled as FNP Clients in the ten participating Scottish Health Boards (HB) since its initiation from 1st January 2010 to 31st March 2016. Eligible women (criteria in Table 1A) are usually referred to the local FNP team after their antenatal booking appointment at around 12 weeks gestation and are required to be enrolled in the programme before 29 weeks. Cases will be identified from the FNP Scottish Information System (FNP SIS).

**Table 1: Maternal baseline characteristics measured at (or before) date of antenatal booking/enrolment table-1:** ^1^Either Health Board level or smaller geographical area such as Community Health Partnership level or where a recruitment area was defined by travel time ^2^Derived by Electronic Data Research and Innovation Service (eDRIS) SMR: Scottish Morbidity Record

A. FNP Clients eligibility criteria	B. Eligibility criteria applied to fields within SMR 02 dataset to identify Controls
1. Living in an FNP-recruiting NHS Health Board	Postcode at antenatal booking mapped onto each FNP recruiting area1
2. First time mothers-to-be (women are eligible if a previous pregnancy resulted in a miscarriage, stillbirth or termination)	No previous live birth
3. Aged 19 years or younger at time of last menstrual period (LMP)	Derived variable2 based on date of birth and date of LMP
4. Less than 28+6 weeks gestation at enrolment into FNP	Gestation at booking date (derived variable2 based on date of booking and date of LMP)

Exclusion criteria

5. Mother-to-be will relinquish baby at birth	Not measurable at recruitment – minimal risk to numbers
6. Moving outside of the FNP catchment area before programme end	Not measurable at recruitment – minimal risk

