#### Controls

The FNP eligibility criteria in Table 1A will be applied to fields in the Scottish Morbidity Record (SMR) 02 Maternity Inpatients and Day Cases dataset to identify potential Controls for each of the areas within the ten participating HBs. Controls’ antenatal booking date will be taken as a proxy for FNP enrolment date (index date). Controls will be women that would have been potentially eligible for FNP, but whose antenatal booking occurred during a period when local FNP teams were not enrolling women. Alongside the eligibility criteria, using the start and end dates of FNP enrolment (including any intervals when cohorts ceased enrolment) provided to us by the FNP SIS, eDRIS will identify individual Controls with antenatal booking dates:

i. in the 12 months prior to initiation of FNP enrolment (Pre-FNP);

ii. in the 12 months post FNP enrolment (Post-FNP);

iii. between periods of FNP enrolment (i.e. when enrolment was temporarily suspended due to caseload capacity, usually up to a maximum concurrent caseload of 25 women, being reached) (Interval).

Further ineligibility criteria are applied to women during the FNP enrolment process, such as planning to place the child for adoption or moving out of the area, but cannot be applied in the selection of Controls as they are not assessed in the SMR02 (or any other dataset) at date of booking.

Within the enrolment period, a second cohort of women exist consisting of women eligible for enrolment into the programme during a period of active FNP enrolment and who:

iv. were approached for FNP but not enrolled to the programme;

v. were not approached (e.g. insufficient capacity in team to offer to all eligible women; near end of enrolment period and caseloads nearly full).

Following advice from the Public Benefit and Privacy Panel (PBPP), it was not possible to access individual level data for these women (in iv and v). However, it is important to note that these groups may have different demographic, social or personal characteristics from those that enrolled in the programme and may differ non-randomly from the Cases for some variables. As it would be beneficial to the evaluation to understand the characteristics of (iv) and (v) above and understand if they differ from Cases and Controls in anyway, aggregate statistics will be provided by eDRIS to the study team. 

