## Discussion

The study protocol is based upon the specification of FNP commissioned by the Scottish Government. This study design is novel for the evaluation of the FNP/NFP programmes which are primarily evaluated with an RCT. However, assessment of effectiveness in evaluation is limited to outcomes available from routinely collected data. The outcomes for this study have been selected by matching routinely collected administrative data to the Scottish FNP logic model, which is based on the underlying programme theory. Therefore, they have been selected on the basis that they are outcomes FNP aims to influence and there is routine data available to assess the outcome. The Controls are well defined and can be identified from routine data sources. However, one limitation is that women who were approached but not enrolled to the programme were removed from the Cases, but those who might have been approached and subsequently not enrolled will still be present in the control group. Since access to these individuals’ data was not permitted, women of similar characteristics in the Controls cannot be identified to remove them. We can however describe these women who did not take up the programme in a period of recruitment (either not approached or not enrolled) and assess if they are different in any way to the case and control groups. If they are not different on the measured factors, then they do not pose a problem. If they are then the potential bias it might bring to the evaluation will be reflected on in the discussion of the main paper.

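### Controls are timed by booking but Cases by enrolment, so Pre-FNP and Interval Controls who book shortly before enrolment opens may be left in the Control group because they did not enrol

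*Protocol article*

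**What the plan says.** **Cases.** Under Identifying Cases and Controls (Cases), a Case is a woman enrolled in FNP, with no condition on her booking date. Referral comes first: eligible women are "usually referred to the local FNP team after their antenatal booking appointment at around 12 weeks gestation". The text of that section sets the upper limit for joining at 29 weeks, and Table 1 words it as "Less than 28+6 weeks gestation at enrolment into FNP".

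**Controls.** Under Identifying Cases and Controls (Controls), the eligibility criteria for area, parity, age and gestation are applied to the maternity records. Timing is then set by booking date, which stands in for the enrolment date. Controls are women "whose antenatal booking occurred during a period when local FNP teams were not enrolling women". The Pre-FNP window is the 12 months before enrolment starts. The Interval window lies between enrolment periods. Both run up to the day enrolment opens, and no gap is stated.

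**Non-enrolled women during enrolment.** The same section describes eligible women who, while enrolment was active, were approached but did not enrol (iv) or were not approached (v). Their individual data could not be accessed, so only aggregate statistics will be supplied.

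**Who is not a Control.** Study design describes Controls as women without FNP support. Data sources and outcomes contrasts women who received FNP with women who did not. Main analyses puts every enrolled woman in the intervention group.

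**Stated limitation.** The Discussion accepts that "those who might have been approached and subsequently not enrolled will still be present in the control group".

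**The concern.** The two groups are placed in time by different events. Between booking and the gestation limit a woman remains eligible for about 17 weeks, and enrolment may open during that time. The Control rule looks only at whether enrolment was open on the day she booked.

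Take a woman who books at 12 weeks, one month before opening. She is about 16 weeks when recruitment starts and could enrol. If she does, she belongs with the Cases. If she declines or is never approached, she stays a Control. Had she booked just after opening, the same outcome would have put her in group (iv) or (v), outside the analysis.

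The late part of each Pre-FNP or Interval window can thus lose its enrollers and keep its non-enrollers. The article itself names differences between enrolled and non-enrolled women as a threat to an unbiased comparison (Analysis, Identification of Cases and Controls). These Controls enter every comparative analysis, and the direction of any bias cannot be known in advance. The rule also sits badly with the Abstract, which describes Controls as pregnant while FNP was not recruiting.

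**Working it through.** The article gives no figure on this point, so there is none to reproduce. The check is date arithmetic.

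**Inputs from the article**
- Booking at about 12 weeks: 12 × 7 = 84 days.
- Enrolment limit of 28+6 weeks: 28 × 7 + 6 = 202 days. The wording in the text (before 29 weeks) gives 203 days.
- Pre-FNP window: 12 months, taken as 365 days, ending at opening.

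**Assumptions not in the article**
- Bookings are spread evenly over each window.
- Interval lengths and uptake *u* are not given, so ranges are shown.
- Every woman still eligible at opening has a real chance to enrol. This makes the results upper bounds.

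**Step 1: time eligible after booking.** 202 − 84 = 118 days, or 16.9 weeks. With the 29-week wording it is 119 days, or 17 weeks.

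**Step 2: share *f* of a window still eligible at opening.** *f* = min(1, days eligible ÷ window length).

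| Booking gestation | Days eligible | Share of Pre-FNP window |
|---|---|---|
| 8 weeks | 146 | 40% |
| 12 weeks | 118 | 32% |
| 16 weeks | 90 | 25% |
| 20 weeks | 62 | 17% |

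| Assumed Interval length (booking at 12 weeks) | Share still eligible at re-opening |
|---|---|
| 118 days or less | 100% |
| 180 days | 66% |
| 270 days | 44% |
| 365 days | 32% |

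**Step 3: effect on the make-up of the Controls.** In an unselected Control group, the share of women who would not enrol if offered FNP is 1 − *u*. If enrollers in the still-eligible part move to the Cases, a fraction *f* × *u* of the bookings leaves and all the non-enrollers stay. Their share becomes (1 − *u*) ÷ (1 − *f* × *u*). For the Pre-FNP window, *f* = 118/365 = 0.323.

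| Assumed uptake | Share if unselected | Share after enrollers leave |
|---|---|---|
| 50% | 50% | 0.5 ÷ (1 − 0.162) = 60% |
| 80% | 20% | 0.2 ÷ (1 − 0.259) = 27% |
| 90% | 10% | 0.1 ÷ (1 − 0.291) = 14% |

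For an assumed 180-day Interval at 80% uptake, *f* = 118/180 = 0.656. The share rises from 20% to 0.2 ÷ (1 − 0.524) = 42%.

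**Step 4: is it corrected elsewhere?** The limitation in the Discussion covers women who would have declined had they been asked, within an otherwise unselected group. It does not cover a window whose enrollers have been taken out. The eligibility checks in the Analysis section compare gestation at enrolment with gestation at booking, but only to test the data fields. The same section keeps all Controls, so no stated step removes these women.

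**The case against.** **Double-counting.** A reader might infer that a woman who books in a closed period and later enrols is counted in both groups. The documents do not support that. Study design, Data sources and outcomes, and Main analyses all place enrolled women on the Case side only, and Cases are matched to the maternity records, so they can be recognised. What is missing is an explicit removal step, which a condensed article may leave to a fuller document. This objection stands. Removing the enrollers, however, is what produces the selection.

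**Booking date as the only criterion.** This would also be too strong. Area, parity, age and gestation apply as well. Only the timing element rests on booking date.

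**Eligible is not the same as contaminated.** The 32% counts women under the gestation limit at opening, not women approached, enrolled or refusing. Referral usually follows booking, and nothing says that teams worked back through earlier bookers. Limited capacity makes it likely that some were never approached, and such women have not selected themselves out by declining. This stands, and is why the figures are upper bounds.

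**Already disclosed.** Would-be decliners among the Controls are an acknowledged limitation, with aggregate comparisons and covariate-adjusted sensitivity analyses planned. This stands in part: the point here is an increment to that bias, but one the limitation does not describe.

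**The remedy has a price.** Dropping all affected Interval Controls could remove the comparators closest in calendar time and shift weight to earlier and later women. This stands and limits the fix.

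**Conclusion.** The point holds and should be fixed. The Control timing rule admits Pre-FNP and Interval women who were still eligible when enrolment opened or re-opened. Once enrollers are counted as Cases, those who remain are selected for not having enrolled, while their counterparts booking after opening are excluded as groups (iv) and (v).

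Up to about a third of Pre-FNP bookings are exposed to this, and all of any Interval of 118 days or less. The bias is better judged by the excess of would-be non-enrollers: at most 10, 7 and 4 percentage points among Pre-FNP Controls at assumed uptakes of 50%, 80% and 90%. It could be larger in short Intervals. These sizes rest on even booking at 12 weeks and on every still-eligible woman having a chance to enrol.

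A reader might take the 32% as the share of Controls who were treated or who refused. The documents support neither, because they give no uptake and do not say how often earlier bookers were approached. Nor can the effect on all of the roughly 6,000 Controls be sized, since the split between Pre-FNP, Interval and Post-FNP Controls is not given. Post-FNP Controls are unaffected unless enrolment reopened.

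**What to change.** 1. In the Controls section, state that a woman enrolled in FNP is never a Control.
2. Using LMP, booking date and the area enrolment dates, all of which the selection already uses, flag every Control who was still under the gestation limit when enrolment opened or re-opened in her area. Report the number by Control type.
3. Restrict Pre-FNP Controls to women whose eligibility window had closed before opening. Shift the 12-month window earlier where the data allow and shorten it where they do not. For an area opening on 1 January 2010, a full window ending 118 days earlier would begin about 5 September 2008. That is before the study population starts on 1 January 2009, so about 365 − 118 = 247 days would remain.
4. For Interval Controls, run the comparison with and without flagged women and report both.
5. Bring the Abstract, Study design, Cases and Controls sections into agreement on how these women are classified.

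**Cost.** The filter is a date calculation and needs no new data. Where the Pre-FNP window cannot be shifted, up to about a third of those Controls are lost, with some loss of precision. The restricted Interval analysis may retain few time-matched Controls, which is why it is reported alongside the full Interval comparison and does not replace it.

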### Identifying children

A mother-child link is available within the SMR02 enabling a flag for children born after the FNP enrolment date (Cases) / antenatal booking date (Controls) to be derived. 

### Data Controllers and Data Processors

#### NHS National Services Scotland (NSS)

NSS is the Data Controller for centrally held health data on Scottish patients made available following approval from the PBPP. Datasets include Outpatient Attendance, Acute Inpatient and Day Case, Maternity Inpatient and Mental Health, Child Health, Birth Record and Accident & Emergency [26]. SMR 02 contains the maternity inpatient and day case data for all women registered to receive maternity health care.

#### Electronic Data Research and Innovation Service (eDRIS)

eDRIS provides a single point of contact to assist researchers in study design, approvals and data access for projects using routinely collected health data in Scotland [27]. The role of eDRIS for this study is to advise on the application submitted to the PBPP, liaise with the trusted third party indexing team (National Record for Scotland, NRS) and the various data controllers on behalf of the study. eDRIS will also oversee all data transfer and linkage to create the study cohort. eDRIS are data processors for this study. The PBPP is a governance structure of NHS Scotland with a remit to carry out information governance scrutiny of requests for linkage and/or access to individual level health data on behalf of NHS Scotland [28].

#### Health Boards (HB)

Each HB in Scotland acts as the Data Controller for the data held on the FNP Scottish Information System (FNP SIS), a national database of FNP data accessible to Family Nurse (FN) teams. Agreement has been sought to allow these data to be processed by eDRIS for this study. Data include both identifiable data that will enable linkage to FNP Clients’ routine data from health, education and social care as well as clinical data recorded by FNs during their visits.

#### Education Analytical Service (EAS) Division

The EAS is a division of the Scottish Government who are data controllers for Education and Social Care data. Requests for data are made through the Data Access Panel. The panel assesses the objectives and data protection implications in relation to each request as well as the security arrangements [29]. 

#### National Records for Scotland (NRS)

The NRS indexing team ensure robust linkage of education data to the research population spine. The pupil census has been matched to the spine to create an anonymised “read-through” index key which NRS and EAS hold at an individual-level.

#### National Services Scotland Safe Haven

NSS is a secure environment in which data are linked and stored. Approved access is provided either remotely or via a secure access point and set up by eDRIS. Both access methods allow trusted and authorised researchers to analyse individual level data while maintaining confidentiality. Remote access to the safe haven is via Citrix software using an accredited organisation’s PC / laptop. The data linkage process is shown in Figure 1.

**Figure 1: Model of pseudonymised data linkage: FNP Scotland Research Database fig-1:**
[figure not shown]

CHSP-Pre-School- Health Visitor first visit (~10 days); 6-8 week review; 27-30 month review; unscheduled review	Contains data on the findings and outcome of the child health reviews for all children in Scotland. Child health reviews incorporate assessment of children's health, development, and wider wellbeing alongside provision of health promotion advice and parenting support.	NHS NSS	✓
CHSP-School - Primary 1 - screening and assessment	A Primary 1 review is offered to all children in Scotland in mainstream and special state schools at the age of 5 as part of the wider child health programme. It contains information on include height and weight measurements, and recording of diagnoses/concerns. Following the primary 1 screening some children have a further assessment which reviews the child's development (e.g. gross motor, fine motor, speech and language, social skills and behaviour).	NHS NSS	✓
FNP Scottish Information System	Contains information on the FNP programme delivery from enrolment in the programme.	Local HBs	✓
School/Pupil Census	Contains information on early learning and childcare provision, pupils, teachers, and school buildings collected from all Local Authority and Grant-aided schools and school centres on publicly funded schools.	SG		✓
Attendance, Absence and Exclusions	Contains information from schools on pupils attendance and absence from schools and the reasons for this. It also includes exclusions.	SG		✓
School Leavers (Summer and Christmas)	Contains information on pupils in each school year who leave school having attained the minimum school leaving age.	SG		✓
Skills Development Scotland: destinations	Contains data on 16-19 year olds in Scotland on school leaver destinations and type of destination (higher education, further education, employment, training, unemployed).	SG		✓
Children and Young People: Looked after children	Each Scottish Local Authority is asked to submit a return providing information on the Looked After Children for which they are responsible.	SG		✓
Children and Young People: Child protection register	Child protection data via the from Local Authorities’ Management Information Systems. The information collected here is the primary national data source on child protection in Scotland.	SG		✓
Scottish Credit and Qualifications Framework	Contains information on the qualifications awarded to learners in Scotland.	SG		✓
Achievement of Curriculum for Excellence levels collections	Achievement of Curriculum for Excellence for all pupils in the stages of Primary (P)1, P4, P7, and Secondary (S)3, who are based on the roll of the school, and for all pupils based in standalone school/units. Each of the following will be collected: Numeracy, Reading, Writing and Listening and Talking.	SG		✓

The specification for this evaluation of FNP requires there be no pre-specified primary outcome(s). The outcomes of this study closely follow the key activities and outcomes in the FNP programme’s logic model [24], covering maternal health, child health and development, and maternal life course and are listed in Table 3.

The ability to report on outcomes will depend on several factors such as geographical and study cohort coverage, data quality (completeness and bias). As a result outcomes have been categorised into either short- or medium-term or descriptive. Short term outcomes (n=25) map well to the logic model, are known to have good data quality, and coverage across Scotland and our study cohort (thus maximising the number that can be formally analysed using statistical methods). These outcomes are likely to be associated with the pregnancy and birth period, and up to the child’s second birthday (e.g. child health outcomes). Medium-term outcomes (n=9) rely on data only measured in the period after the second birthday (e.g. school-based outcomes at age four-years of age onwards) and the population included in the analysis would be restricted as a result. These short- and medium-term outcomes will be formally analysed using statistical modelling and will compare between participants who did (Cases) and did not receive FNP provision (Controls).

Descriptive outcomes (n=20) are those where the direction of the FNP effect is either uncertain, outcomes are rare, or where the data are classed as experimental statistics (i.e. a type of official statistic that is undergoing development such as child attainment).

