### Study population

The population will be all women eligible for the FNP Programme from 1st January 2009 to 31st March 2016 and their first-born child(ren). 

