Binary outcomes will be modelled using a logistic model and presented as odds ratios comparing the odds of an event in a case compared with the Control. For continuous outcomes a multilevel linear model will be fitted and results presented as a difference in means (Case minus Control group). Time to event analyses (e.g. cessation of breastfeeding, time to subsequent birth) will be analysed using a proportional hazards regression model and results presented as hazard ratios. We will ascertain if the proportional hazards assumption has not been violated by inspecting the log (-log(survival)) plot and Schoenfeld residuals. Count data will be analysed using a Poisson multilevel model. If the distribution of events display signs of over dispersion (greater variance than might be expected in a Poisson distribution), then a Negative Binomial model will be used. Results will be presented as the incidence rate ratio in the case arm compared to the Control group. The impact of FNP visits (dosage of intervention) on outcomes will be explored as a sensitivity analysis. Adherence will be defined as the number of FNP visits that a Client received during their programme enrolment overall or by phase (pregnancy, infancy, toddler), dependant on outcome. A number of other sensitivity analyses are proposed including adjustment for any imbalance in confounders (pre-exposure maternal and baby characteristics) (note that these will be assessed for the differing denominators (study populations) dependent on outcome) and adjustment for multiple testing.

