### Study timelines

The study started in July 2016, data will be made available for analysis to begin in January 2020 and will report to the Scottish Government in 2020. 

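### For school-age outcomes, the age restriction falls unequally on Cases and Control types, and the main model is not stated to adjust for calendar time

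*Protocol article*

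**What the plan says.** **Outcomes.** Under Data sources and outcomes, nine medium-term outcomes rely on measurements after the second birthday, with school measures from age four as the example, "and the population included in the analysis would be restricted as a result". They are to be formally compared between Cases and Controls.

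**Groups.** The study population is "all women eligible for the FNP Programme from 1st January 2009 to 31st March 2016". Cases are women enrolled "since its initiation from 1st January 2010 to 31st March 2016". There are three types of Control:
- Pre-FNP Controls booked in the year before local enrolment opened.
- Post-FNP Controls booked in the year after it closed.
- Interval Controls booked "between periods of FNP enrolment".

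Local opening and closing dates come from the programme's information system and are not in the article.

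**Follow-up.** Study timelines states that "data will be made available for analysis to begin in January 2020".

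**Model.** Main analyses specifies multilevel models with clustering by Health Board and team/cohort. Effects over time and between areas are also examined, using group-by-year interactions. Adjustment for imbalanced confounders is listed among the sensitivity analyses ("note that these will be assessed for the differing denominators (study populations) dependent on outcome"). The baseline table under Descriptive analysis includes Health Board, age and gestation at booking, but no booking date, birth year or school year.

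**The concern.** A limit on child age is a limit on calendar date of birth, and the groups are defined by calendar date. In every area Pre-FNP Controls come first and Post-FNP Controls last. When the limit binds, it does not thin the groups evenly.

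Two things can follow. Where Pre- and Post-FNP Controls would have bracketed the Cases in time, losing the later ones leaves Cases compared mainly with earlier births, so a drift in a school measure can look like a programme effect. Where an area opened late, its Controls may stay in the analysis with few or no Cases. That area then informs the effect mainly through comparison with other areas. Balance on the listed covariates could look good in both situations, because none of them records calendar time.

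**Working it through.** The article gives no sample size, cut-off or retention share for these outcomes, so there is no figure to reproduce. The check is date arithmetic.

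**Inputs from the article**
- Cases enrolled 1 January 2010 to 31 March 2016.
- Booking at around 12 weeks; Case enrolment before 29 weeks.
- School outcomes from age 4; Primary 1 review at age 5.
- Data available January 2020, which is the latest possible end of follow-up.

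**Assumptions**
- Birth at 40 weeks, so 28 weeks after a Control's booking.
- Case enrolment at about 18 weeks, so birth 22 weeks later (range: enrolment at 12 to 28 weeks).
- Uniform accrual.
- Data cut on 1 January 2020, with earlier cuts as sensitivity.

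**Formulas.** Last birth = data cut − outcome age. Last Control booking = last birth − 196 days. Last Case enrolment = last birth − 154 days. Share kept = days of the window up to that date ÷ days in the window.

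**Cut-offs, data to 1 January 2020**

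| Outcome age | Last birth | Last Control booking | Last Case enrolment |
|---|---|---|---|
| 4 | 1 Jan 2016 | 19 Jun 2015 | 31 Jul 2015 |
| 5 | 1 Jan 2015 | 19 Jun 2014 | 31 Jul 2014 |

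**Cases kept overall**
- Age 4: 2038/2282 days = 89% (87% to 92% over the enrolment range).
- Age 5: 1673/2282 = 73% (71% to 76%).
- With a data cut of 31 December 2018: 73% at age 4 and 57% at age 5.

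**Pre-FNP Controls.** All are kept in any area that opened by about 20 June 2015 (age 4) or 20 June 2014 (age 5), because their window closes the day before opening.

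**Post-FNP Controls**
- Enrolment closed 31 March 2015: 80/366 = 22% kept at age 4, 0% at age 5.
- Enrolment ran for 12 months from mid-2012: 100% at age 4, 354/365 = 97% at age 5.
- Enrolment ran for 12 months from mid-2011: 100% at both ages.

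**Late-starting areas (illustrative dates, Cases to 31 March 2016)**

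| Opened | Age | Data cut | Pre-FNP kept | Cases kept |
|---|---|---|---|---|
| 1 Jul 2013 | 5 | 1 Jan 2020 | 100% | 396/1005 = 39% |
| 1 Jul 2014 | 5 | 1 Jan 2020 | 354/365 = 97% | 31/640 = 5% |
| 1 Jul 2014 | 5 | 30 Sep 2019 | 261/365 = 72% | 0% |
| 1 Jul 2015 | 4 | 1 Jan 2020 | 354/365 = 97% | 31/275 = 11% |
| 1 Jul 2015 | 5 | 1 Jan 2020 | 0% | 0% |

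**Loss of bracketing, one example.** Take an area enrolling from 1 July 2013 to 31 March 2015, with equal numbers of Pre- and Post-FNP Controls and no Interval Controls. Unrestricted, the Control windows centre on 30 December 2012 and 30 September 2015. Their average is 16 May 2014, which is also the centre of the Case window. At age 5 no Post-FNP Controls remain, and the kept Cases (1 July 2013 to 31 July 2014) centre on 14 January 2014. That is 380 days after the Pre-FNP centre. Subtracting the 42-day difference between the booking-to-birth and enrolment-to-birth gaps leaves 338 days, or about 11 months in date of birth.

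**27-30 month review.** At 30 months with data to 1 January 2020, the last Control booking falls in December 2016, after the study population closes. Nobody is lost.

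**The case against.** The strongest reply has four parts.

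**The imbalance is easily overstated.** A reader might infer that all Post-FNP Controls are lost, that all nine comparisons become before-after, and that late-starting areas supply Controls only. The documents support none of these as general statements:
- Post-FNP windows follow local closing dates that are not given, and areas that closed early keep theirs. An area that enrolled until 31 March 2016 has no Post-FNP Controls within the study population for the restriction to remove.
- Interval Controls are contemporaneous with Cases, so a before-after reading requires them to be absent. Their number is not given.
- Controls-only areas need particular opening dates. Dating Cases by enrolment rather than booking, a July 2014 opening still keeps about 5% of Cases at age 5 with a January 2020 cut. Areas that opened later still can lose both groups.
- How many of the nine outcomes are school-age cannot be seen from the text at hand.

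**Losing late Cases is not harmful in itself.** Within an area it brings the remaining Cases closer in time to the Pre-FNP Controls. The harm comes from losing the later Controls and from the changed mix of areas.

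**The plan has relevant provisions.** It names geographical and cohort coverage as limits on reporting, models clustering by area, and examines group-by-year interactions, which would ordinarily carry a year term. This mitigates the concern but does not remove it. The interaction is described as an additional look at effects over time, not as the main estimate. Clustering terms do not supply Cases to an area that has none. Adjustment by outcome denominator is a sensitivity analysis on covariates without calendar time.

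**A detailed analysis plan is promised.** Exact cut-off dates do belong there, and their absence is no fault. The point rests on what the article itself fixes: the Control windows, the restriction, the covariate list and the secondary status of adjustment.

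**Conclusion.** The point holds for medium-term outcomes measured at about 4 to 5 years. With data to January 2020, the restriction keeps most Pre-FNP Controls while removing Cases enrolled after about July 2015 (age 4) or July 2014 (age 5), and any Post-FNP Controls booked after about June of the same years. The direction follows from the group definitions alone. The size rests on term birth, uniform accrual, enrolment at about 18 weeks and the data cut; an earlier cut makes the loss larger.

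How many areas keep Controls with few or no Cases depends on dates the article does not give, so this is a possibility to check. The resulting bias cannot be put in figures, since no trend in any outcome is given and its direction would depend on that trend. As the main analysis is described, calendar time and area differences can enter the estimated effect of FNP on these outcomes.

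**What to change.** For each school-age outcome:
1. Derive the last index date at which a child can reach the measurement age, separately for booking (Controls) and enrolment (Cases), or equivalently a single last date of birth.
2. Include only areas with both Cases and Controls before that date.
3. Put birth or school year, and area, in the main model.
4. Tabulate Cases and Pre-FNP, Interval and Post-FNP Controls by area.
5. Describe the comparison as before-after in areas where no Interval or Post-FNP Controls remain.

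A comparison restricted to equal-length windows either side of the local opening date is best kept as a sensitivity analysis.

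The cost is some wording and a filter on dates already needed to define the groups. The downside is somewhat fewer Controls or areas, and slightly wider intervals for these outcomes.
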